### Sample size

This study will aim to recruit approximately 30 participants. This sample size was chosen as it is a realistic target when considering cervical cancer incidence both in the UK and at UHL where recruitment will take place over the given time period. In line with recommendations from the National Institute for Health Research, a sample size of 30 is appropriate to answer the questions posed by a feasibility trial.^32^ The feasibility of lifestyle and PA interventions in endometrial and breast cancer survivors have successfully employed similar sample sizes.^27 33^

### Intervention

The aim of the multicomponent intervention is to increase PA levels of the target population, specifically, individual and group-based walking over 12 consecutive weeks (figure 1). Table 2 provides a description of each intervention component while figure 2 outlines the Logic Model. Walking has been identified as a common PA preference among gynaecological cancer survivors,^34^ particularly for those who do not meet the recommended PA guidelines.^35^ The intervention components are underpinned by social cognitive theory,^36^ and are informed by the health belief model,^37^ and theories of self-regulation.^28^ Self-monitoring behaviour is strongly linked with successful PA behaviour change, particularly when combined with at least one other self-regulatory component.^38^ The intervention includes education provision, problem-solving and goal setting in relation to increasing PA levels after treatment for cervical cancer. Self-monitoring of PA behaviour will be facilitated by providing participants with an intervention diary to complete daily and weekly, fortnightly online health coaching via video or telephone call administered by the study coordinator and a consumer PA monitor (*fitbit inspire 2*) to receive real-time feedback on their activity levels and prompts to be more active and to review goals. Throughout, peer support and group walking among participants will be encouraged via a messaging platform, which will allow participants to maintain contact and organise group walking sessions. The study coordinator will suggest appropriate walk locations convenient to each group.

**Table 2 T2:** Description of intervention components

Intervention component	Description
*Intervention launch*	**Education** (interactive session facilitated by the study coordinator, delivered virtually) What is meant by PA? What kinds of activities count as PA? What does moderate intensity PA feel like? What benefits are associated with PA? Knowledge of PA recommendations How many steps per day should you aim for? **Barrier Identification** Is there anything that might stop you from being physically active? How can you overcome these challenges? **Goal Setting** Introduction to SMART goals Using PA monitor to set goals related to steps and intensity *Each section divided by guided ‘stand up and stretch’ prompts
*Self-monitoring of PA*	The PA monitor will provide participants with feedback on their activity levels via: number of steps taken by participants and the number of minutes that participants spend in a moderate intensity activity each day
*Prompts*	Prompts offered by PA monitor to encourage PA Prompts to update participant on their progress in reaching their daily goal
*Intervention diary (monitoring of well-being*)	**Daily entries** Input daily step count as shown on PA monitor Rate mood out of 10 **Weekly entries**
	Rate the following symptoms on a traffic light system: energy levels, anxiety levels, body confidence, physical pain, bladder issues
*Health coaching*	Revision of previous goal(s) and the outcome (successful/ unsuccessful); attribute reasons for this outcome Identification of challenges and facilitators regarding previous goal Revision of steps, intensity and well-being over the previous 2 weeks Facilitated goal setting and identification of potential challenges for the following 2 weeks
*Group messaging*	To be used as a platform to schedule group walks (organising a time and a place) with the aim of one group walk per week. Standardised communication prompts to be offered by the study coordinator
*Online community*	Participants will be encouraged to use the study-specific community on the PA monitor application, accessed via smart phone where personal PA insights and statistics can be shared with other participants

PA, physical activity.

**Figure 1 F1:**
[figure not shown]
Intervention programme flow chart.

**Figure 2 F2:**
[figure not shown]
Logic model for the ACCEPTANCE trial. PA, physical activity; SCT, social cognitive theory.

### Measures

All PA and health measures will be assessed at baseline, week 12 and 3 months after completion (week 24). Previous literature suggests that psychological measures may take longer to change than physical measures (e.g., menopausal symptoms or PA) and therefore to reduce participant burden, only these will be taken at week 6 (table 3).

**Table 3 T3:** PA and health outcomes, outcome measures and measurement time points

Measures	Assessment tool	Baseline	Week 6	Week 12	Week 24
Device-assessed PA	Accelerometer	x	x	x	x
Menopausal symptoms	MRS	x	x	x	x
Quality of life	EORTC-QLQ-30	x		x	x
Depression and anxiety	HADS	x		x	x
Fatigue	MSFI-SF	x		x	x
Walking self-efficacy	Self-efficacy for Walking scale	x		x	x
Motivation for exercise	BREQ-3	x		x	x
Enjoyment of PA	PACES	x		x	x

BREQ-3, Behavioural Regulation in Exercise Questionnaire; EORTC-QLQ-30, European Organisation of Research and Treatment of Cancer Core Quality of Life Questionnaire; HADS, Hospital Anxiety and Depression Scale; MFSI-SF, Multi-dimensional Fatigue Symptom Inventory; MRS, Menopausal Rating Scale; MSFI-SF, Multidimensional Fatigue Syndrome Inventory- Short Form; PA, physical activity; PACES, Physical Activity Enjoyment Scale.

#### PA and health measures

An accelerometer (GENEActiv, Activinsights) and sleep log will be administered at all evaluation time points to measure PA. Participants will be asked to wear the accelerometer on their non-dominant wrist 24/7 for 8 days at each time point. Valid data will be at least 3 days >16 hours of accelerometer data collected.^39^ Device-assessed PA will be the primary research outcome measure of interest in the subsequent pilot study and definitive main trial.

Participants’ belief in their ability to successfully complete incremental 5–50 min periods of walking at a moderate/brisk pace will be assessed via the self-efficacy for walking scale.^40^ Motivation for PA will be assessed using the Behavioural Regulation in Exercise Questionnaire.^41^ This is a 23-item scale which assesses motivation on a self-determination continuum. Enjoyment of PA will also be assessed via the original 18-item PACES scale.^42^

In relation to well-being, menopausal symptoms, such as hot flushes and sweating will be investigated using the Menopausal Rating Scale.^43^ Quality of life will be assessed using the EORTC QLQ-30, which is commonly used in gynaecological cancer populations and includes five functional scales, three symptom scales, a global health scale and a quality of life scale. The Hospital Anxiety and Depression scale (HADS),^44^ will be administered to measure symptoms of anxiety and depression. Fatigue will be assessed using the Multi-dimensional Fatigue Symptom Inventory (MFSI-SF),^45^ a measure which has been previously used to assess fatigue in a gynaecological cancer population.^23^

#### Evaluation-related feasibility measures

Participant recruitment rates will be monitored by recording the number of identified potential participants, the number of those who express an interest in taking part, the number of those who are eligible and not eligible along with the reasons for ineligibility and the number who consent to participate. Retention and attrition rates will be monitored by recording the number of participants who withdraw from the study and the number who do not attend follow-up. Where possible, reasons for withdrawal will also be reported. The number of participants who complete the PA and health measures at each time point will be summarised.

### Process evaluation

The process evaluation will be conducted to explore participant experiences of the study and intervention as well as compliance with the intervention components, to identify facilitators and barriers to increasing PA and any suggestions for improvement and refinement. Compliance with intervention components will be reviewed throughout the intervention. Data will be presented on launch attendance rates, the number of diary entries completed, number of daily step counts recorded to reflect compliance of wearing the PA monitor, number of health coaching sessions attended, the number of participants who post on the online forum and engage in group messaging, the number of participants who take part in group walks and the frequency of these.

Questionnaires will be administered to understand participants' experience of attending the intervention launch, of using the PA monitor and the group messaging. A semi-structured interview will also be conducted by the study coordinator to further explore perceptions of the intervention and the evaluation measures, perceived benefits of participation, maintenance of the intervention components and PA levels. Interview data will be analysed using Template Analysis,^46^ employing a deductive coding framework to inform study refinement. To ensure a balanced insight and that subsequent meaningful refinement can be implemented, some transcripts will be coded by an independent researcher who did not contribute to the intervention design.

A researcher log will be completed by the study coordinator where a record of interactions with participants (e.g., email conversations/telephone conversations) will be kept throughout the duration of the study. Feedback will be broadly divided into four categories: evaluation of intervention components; experience of evaluation measures; alterations to future intervention implementation; barriers to PA and reasons for discontinuation (where relevant).

### Data collection

The accelerometer and the quantitative measures will be posted to participants. Process evaluation questionnaires will be completed online throughout the intervention. The evaluation interview will be offered after the week-24 time point to all participants (including those who have withdrawn) either in person or via video call.

### Statistical analysis

As this is a feasibility study, main analyses will use descriptive statistics. Data will be analysed using *IBM SPSS statistics V.25*.

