## Methods and analysis

### Study design

This is a single-arm pre study and post study to assess the feasibility and acceptability of conducting and evaluating a PA intervention following treatment for cervical cancer. A process evaluation will also be conducted throughout the study.

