#### The feasibility of study recruitment and retention

A priori, we have defined a recruitment success rate as recruitment of 30 participants in the first 3 months or that 75% of those identified as eligible are recruited, and a successful retention rate at week-24 as 70%.

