#### The feasibility of and compliance with intervention components

Attendance rates at the intervention launch, engagement with the online forum, frequency of wearing the PA monitor, frequency of group walking sessions, compliance with diary completion and attendance rates at health coaching sessions will all be summarised. The threshold of feasibility for these rates will be 70% of participants complying, respectively.

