#### The feasibility of the evaluation measures

Compliance with evaluation measures will be deemed successful if no more than 20% of participants fail to provide questionnaire and accelerometer data at both baseline and week-24 follow-up.

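### Feasibility rates from about 30 women are judged met or not met on the observed percentage, with no interval planned; reporting each with a 95% CI is a cheap improvement

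*Protocol article*

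**What the plan says.** The design is stated under Study design: "This is a single-arm pre study and post study to assess the feasibility and acceptability". On size, the Sample size section says "This study will aim to recruit approximately 30 participants" and, citing a general recommendation, that "a sample size of 30 is appropriate to answer the questions posed by a feasibility trial". It gives no precision target.

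The Statistical analysis section opens with "As this is a feasibility study, main analyses will use descriptive statistics". Its subsections then set the criteria:

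- **Recruitment:** "recruitment of 30 participants in the first 3 months or that 75% of those identified as eligible are recruited".
- **Retention:** "a successful retention rate at week-24 as 70" per cent.
- **Intervention components:** "The threshold of feasibility for these rates will be 70% of participants complying, respectively".
- **Evaluation measures:** "Compliance with evaluation measures will be deemed successful if no more than 20% of participants fail to provide questionnaire and accelerometer data" at baseline and week 24.

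No confidence interval and no intermediate zone is given for any of these. The limitation on statistical power, in the strengths and limitations box and again in the Discussion, concerns changes in physical activity and other outcomes. It does not concern the feasibility rates.

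**The concern.** The feasibility proportions are what this study is for, and the article itself fixes how they are judged: an observed percentage against a single cut-off. A rate just above the line and a rate just below it receive opposite labels, although about 30 women can hardly tell them apart. Nothing in the printed plan shows the reader how wide the uncertainty is.

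What is at stake is the next trial, which the Ethics and dissemination section says these results will inform. Retention, for example, determines how many women must be recruited to leave a given number at follow-up. If only the point estimate is carried forward, that trial is planned as though the rate were known.

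**Working it through.** **Is there a figure to reproduce?** No. The target of about 30 has no significance level, power, effect size or interval width behind it. The check is therefore of the precision that 30 gives at the stated cut-offs. The two-sided 95% level is my assumption, because the article states none.

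**Inputs**

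- n = 30 (Sample size).
- Retention and each compliance rate: 70% of 30 = 21, so the rule is at least 21/30.
- Completeness: at most 20% of 30 = 6 failing, so at least 24/30.
- Uptake has the number of eligible women as denominator. If 30 are recruited at exactly 75%, that number is 30/0.75 = 40. The 40 is illustrative; the article does not give it.

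**Step 1: precision at each cut-off.** The exact (Clopper-Pearson) limits for x of n are the 2.5% quantile of Beta(x, n − x + 1) and the 97.5% quantile of Beta(x + 1, n − x). Wilson limits are a cross-check.

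| Observed | Exact 95% CI | Wilson 95% CI |
|---|---|---|
| 21/30 = 70% | 50.6% to 85.3% | 52.1% to 83.3% |
| 24/30 = 80% | 61.4% to 92.3% | 62.7% to 90.5% |
| 30/40 = 75% | 58.8% to 87.3% | 59.8% to 85.8% |

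The two exact intervals at n = 30 are 85.3 − 50.6 = 34.7 and 92.3 − 61.4 = 30.9 points wide. For comparison, 20/30 (67%), which fails the 70% criterion, has an exact interval of 47.2% to 82.7%, almost the same as that of 21/30, which passes.

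**Step 2: how often each rule is satisfied.** With X ~ Binomial(30, p), the chance of passing is P(X ≥ 21) for the 70% rule and P(X ≥ 24) for the 80% rule.

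| True rate p | Passes 70% rule | Passes 80% rule |
|---|---|---|
| 50% | 2.1% | 0.1% |
| 60% | 17.6% | 1.7% |
| 65% | 35.8% | 5.9% |
| 70% | 58.9% | 16.0% |
| 75% | 80.3% | 34.8% |
| 80% | 93.9% | 60.7% |
| 85% | 99.0% | 84.7% |
| 90% | 100.0% | 97.4% |

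The 70% rule therefore passes a true 60% with probability 17.6%, and fails a true 75% with probability 100 − 80.3 = 19.7%. The 80% rule passes a true 70% with probability 16.0%, and fails a true 85% with probability 100 − 84.7 = 15.3%. Further away the 70% rule works well: 2.1% pass at a true 50% and 99.0% at a true 85%.

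**Step 3: what it means for planning.** To keep a fixed number of women at follow-up, recruitment scales as 1/retention. If 21/30 were observed, planning on the lower limit instead of the point estimate needs 0.700/0.506 = 1.38 times as many recruits. Planning on the upper limit needs 0.700/0.853 = 0.82 times as many. The point estimate alone hides that range.

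**The case against.** The case against is substantial, and much of it stands.

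- **An analysis plan that is not shown may add intervals.** Descriptive statistics do not exclude a CI on a proportion, and a journal article need not list every tabulated quantity. This is fair, and it keeps the point small. What remains is that the article prints the decision criteria themselves, and those are read from the point estimate.
- **The article claims no level of certainty.** A reader might infer that the plan overstates how sure its verdicts are. It does not say so, and calling 30 appropriate for a feasibility trial is not a precision claim.
- **The rules do discriminate.** A reader might infer that 30 women cannot tell good rates from bad. Step 2 shows otherwise for rates 15 to 20 points from the 70% cut-off. The weakness is local, and the article nowhere calls 60% unacceptable or 75% clearly good.
- **One participant can change a verdict at any threshold and any sample size.** This is true. Nor does the article say that one missed criterion stops the programme: reasons for withdrawal, interviews and the researcher log also feed the judgement.
- **No joint pass is required.** A reader might multiply pass probabilities across the intervention components. The article applies the 70% threshold to the components respectively, so that calculation does not bear on the plan.
- **Recruitment is different.** Its rate has its own denominator, and its alternative route is a count within 3 months. The n = 30 argument applies strictly to retention, compliance and completeness.

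**Conclusion.** The point holds as a cheap improvement. Retention, each compliance rate and completeness of measures are judged on observed percentages, and no interval is mentioned. At the cut-offs the exact 95% CIs with 30 women are about 31 to 35 points wide, and the 70% rule gives the unintended verdict about one time in five when the true rate is 60% or 75%.

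These figures assume exactly 30 women in each denominator, independent participants and a two-sided 95% level. With fewer recruits the intervals would be wider. The documents do not support the stronger conclusions that the sample size is wrong, that a descriptive analysis is unsuitable, or that the cut-offs are unusable.

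**What to change.** In the Statistical analysis section and its subsections on recruitment and retention, intervention components and evaluation measures:

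1. State that every feasibility proportion is reported with an exact or Wilson 95% CI, including uptake among eligible women with its own denominator.
2. Keep the existing cut-offs as targets for the observed rate.
3. Beside each met or not-met verdict, state whether the CI includes the cut-off.
4. State that the CI limits, not only the point estimate, are carried into planning of the next trial.

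A criterion counted as met only when the lower CI limit reaches the cut-off is not advised. It would require 27/30 for the 70% criteria and 29/30 for the 80% criterion, and a true retention of 80% would then be called met only about 12% of the time.

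The cost is a few sentences and minutes of analysis. Sample size, cut-offs and participant procedures do not change. The downside is that results near a cut-off will read as less conclusive.

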#### The feasibility of inclusion criteria

We have suggested that if an eligibility criterion accounts for 40% of ineligibility, it will be reported.

#### The feasibility of study recruitment and retention

A priori, we have defined a recruitment success rate as recruitment of 30 participants in the first 3 months or that 75% of those identified as eligible are recruited, and a successful retention rate at week-24 as 70%.

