#### Objectives

To determine participant recruitment, retention and attrition rates.To review descriptive data to determine the feasibility of the inclusion criteria.To determine compliance and completeness of evaluation measures at all time points.To report the feasibility of delivering the intervention and evaluation measures.To explore participant compliance with the intervention.To obtain views on the acceptability of the intervention and evaluation measures.To describe device-assessed PA levels and questionnaire data outcomes of interest.

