### Participants and recruitment

Participants between the ages of 18 and 60 years who have undergone treatment for cervical cancer at least 6 months previously with curative intent (either surgery, chemoradiotherapy or both modalities), who do not meet the national PA guidelines (150-300 min of moderate to vigorous intensity PA per week),^30^ who can gain permission from their gynaecologist/oncologist to take part and are proficient in speaking English will be recruited. The age range of 18–60 years was chosen to reflect the Chief Medical Officer’s PA adult guidelines and to optimise engagement and adherence to a technology-based PA programme. Exclusion criteria are benign or premalignant (cervical interepithelial neoplasia) disease of the cervix; clinical/radiological evidence of disseminated malignancy; pregnancy or breast feeding; performance status ≥3; comorbidity that in the opinion of the patient’s supervising gynaecologist/oncologist would preclude the patient from meeting the study requirements.

Initial database screening will take place by the clinical gynaecological oncology team to identify candidates who are at an appropriate age and stage in their treatment journey. Potentially eligible participants will be approached through their clinical team; recruitment posters will be placed in the gynaecological and oncology outpatient departments at UHL; and study details (overview of research, inclusion criteria and relevant contact details) will be posted on social media platforms. Local cervical cancer support groups will also be contacted and given information on the study to raise awareness of the research. Screening will take place via a telephone call with a member of the research team. The Scottish Physical Activity Questionnaire^31^ will be used to determine PA levels. Participants will be asked how many minutes per week they spend being active at a moderate intensity in the context of the last 7 days. Consent procedures will take place either virtually via video/telephone call or in person at UHL.

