### Ethics and dissemination

Ethical approval has been granted by the West of Scotland Research Ethics Committee 1 for this study. Results will primarily be used to refine intervention components and to inform a larger full-scale trial, if appropriate. Results from the study will be shared in peer-reviewed journals, presented at international conferences and will be shared with the UHL and Leicester Hospital’s charity.

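### The 75% uptake branch of the recruitment criterion has no minimum number and no time window, yet it can stand in for the target of 30 women

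*Protocol article*

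**What the plan says.** Under Statistical analysis (The feasibility of study recruitment and retention), the protocol article sets the success rule a priori: "recruitment of 30 participants in the first 3 months or that 75% of those identified as eligible are recruited". The period of 3 months is attached to the first branch only.

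The Sample size section states "This study will aim to recruit approximately 30 participants" and gives as a reason that "it is a realistic target when considering cervical cancer incidence both in the UK and at UHL". The same sentence mentions a recruitment period, but the article does not give its length and does not tie it to the 75% branch.

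Eligibility is settled late: "Screening will take place via a telephone call with a member of the research team" (Participants and recruitment). The counts to be recorded include "the number of those who are eligible and not eligible along with the reasons for ineligibility and the number who consent to participate" (Evaluation-related feasibility measures).

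The rule serves the first listed objective, "To determine participant recruitment, retention and attrition rates". The results are to be used for refinement and "to inform a larger full-scale trial, if appropriate" (Ethics and dissemination).

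**The concern.** The two branches measure different things. Thirty women in 3 months tests supply: can enough women be found, and quickly enough? Seventy-five per cent of eligible women tests willingness among those who were found. The connector lets the second replace the first.

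Because the uptake branch has no floor, it can be met by a handful of women. Because it has no window, it can be met at any time. The stated reason for choosing 30 is that this number is realistic given incidence and the local hospital, so supply is one of the things the study should show. A success verdict reached through the uptake branch could leave that unanswered and still be carried forward to the planning of a larger trial.

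**Working it through.** **Inputs from the protocol article.** Branch A: 30 recruited within 3 months. Branch B: recruited/eligible at least 0.75. Connector: or. Target: about 30. The 30 is a pragmatic figure with no formula behind it, so there is no calculation to reproduce.

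**Inputs that are assumptions.** The numbers of eligible women, the durations and the true uptake values below are illustrative. The protocol gives none of them.

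**Step 1. Apply the rule as written.**

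| Eligible | Recruited | Months | A met | B met | Verdict |
|---|---|---|---|---|---|
| 8 | 6 | 3 | no | yes (75%) | success |
| 8 | 6 | 12 | no | yes (75%) | success |
| 40 | 30 | 12 | no | yes (75%) | success |
| 40 | 30 | 3 | yes | yes (75%) | success |
| 45 | 29 | 3 | no | no (64%) | not a success |

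Six recruits are 6/30 = 20% of the target and pass. Twenty-nine recruits in 3 months, one short of the target, do not pass if 45 women were eligible.

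**Step 2. Precision of an observed 75%** (exact Clopper-Pearson 95% intervals).

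| Recruited/eligible | 95% interval |
|---|---|
| 3/4 | 19% to 99% |
| 6/8 | 35% to 97% |
| 9/12 | 43% to 95% |
| 15/20 | 51% to 91% |
| 30/40 | 59% to 87% |

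The last row is the smallest denominator at which 30 recruits correspond to exactly 75%: 30/0.75 = 40.

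**Step 3. Chance of meeting branch B alone when true uptake is below 75%.** With k eligible women and true uptake p, the chance is P(X ≥ ⌈0.75k⌉), X ~ Binomial(k, p).

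- k = 4, p = 0.60: 4 × 0.6³ × 0.4 + 0.6⁴ = 0.3456 + 0.1296 = 0.475.
- k = 8, p = 0.50: (28 + 8 + 1)/256 = 37/256 = 0.1445, or 0.14.

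| k | Needed | p = 0.60 | p = 0.50 |
|---|---|---|---|
| 4 | 3 | 0.475 | 0.31 |
| 8 | 6 | 0.315 | 0.14 |
| 12 | 9 | 0.225 | 0.07 |
| 20 | 15 | 0.126 | 0.02 |
| 40 | 30 | 0.035 | 0.001 |

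**Step 4. Limits of step 3.** Every k in the table is a multiple of 4, where 75% can be hit exactly and the chance is locally highest. At p = 0.60 the chance is 0.216 with 3 women, 0.159 with 7 and 0.119 with 11. The decline with k is real but sawtoothed. It also depends on true uptake being below 75%: at p = 0.85 the branch is met more often with 40 women (0.97) than with 4 (0.89).

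**Step 5. The full rule, with branch A included.** If all eligible women are found within 3 months and p = 0.60, the chance of reaching 30 recruits is 0.56 with 50 eligible, 0.96 with 60 and above 0.99 with 70.

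**The case against.** **A low count cannot be hidden.** This stands in part. Numbers eligible and consented are recorded, the main analyses are descriptive, and no section makes this rule a binding condition for the next trial. A reader would see 3 of 4. But the authors set a numerical threshold in advance so that the verdict would not be a matter of later judgement, and reporting the counts does not correct a verdict that the rule has already given.

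**Very small pools are unlikely.** The protocol plans database screening, approach through clinical teams, posters, social media and support groups. Four eligible women is an extreme example and is not predicted by the documents. The late-recruitment case, 30 of 40 well after month 3, does not need a small pool.

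**The 3 months may be meant for both branches.** The wording does not read that way. If it were so, the window problem would go, but the missing minimum would remain.

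Two stronger readings are tempting, and the documents do not support them.

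- *A reader might infer that poor supply makes a success verdict more likely overall.* It does not. Under the full rule good supply passes far more often: 0.96 with 60 eligible women at 60% uptake, against 0.475 with 4. The inverse pattern belongs to the uptake branch alone, below 40 eligible women and with true uptake below 75%.
- *A reader might infer that 30 women in 3 months at low uptake, say 30 of 100, is a false success, so both tests must be met.* That recruitment meets the study's only numerical target, and no section says that a later trial needs 75% uptake. Requiring both would fail 30 of 41 in 3 months (73%). Low uptake there raises a question of selection and generalisability. Nor do the counts show that women who were eligible but not recruited had declined.

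**Conclusion.** The concern holds for the uptake branch. It has neither a minimum number nor a time window, yet it may replace the target of 30 in 3 months. Followed exactly, the rule calls 3 of 4 or 6 of 8 eligible women a recruitment success, and likewise 30 of 40 reached at any later date. That these cases pass follows from the wording and needs no assumption. How often the branch would be met by chance does rest on assumed uptake and pool sizes, so those probabilities are illustrations only.

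This is a defect in a rule that the protocol states, not a detail left to a fuller document. It affects the label put on the recruitment result and has no consequence for participants or for the data collected. It should be fixed, and it does not undermine the study.

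**What to change.** Replace the single either/or rule with two verdicts, reported separately over the same stated recruitment window:

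- (a) the number recruited in the first 3 months, against 30;
- (b) uptake among eligible women, against 75%, with numerator and denominator.

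State a minimum number of women below which (b) alone does not count as recruitment success. The investigators should choose that number and give the reason for it.

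If (a) is met with low uptake, report this as a concern about selection and generalisability, not as an automatic failure. If (a) fails and (b) is met, say that supply or pace was the problem.

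The cost is the rewording of one criterion. The counts are already to be recorded. The downside is that the criterion becomes somewhat harder to meet.
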